### Developing the implementation toolkit

The accompanying toolkit aims to minimise barriers to use and optimise the implementation of the VR training. We will integrate the findings from the development of the VR training package with data collected from 20 interviews with senior care home staff who have experience with VR training and staff from companies that provide VR training. This will inform discussions with our PPIE group to develop the toolkit. We will also create a logic model of the training and test assumptions of potential accompanying tools and resources with the PPIE group to finalise the delivery method.

#### Setting, participants and recruitment

Up to 20 semi-structured interviews will be conducted remotely (via Microsoft Teams or telephone) or in-person at participants’ workplaces, such as company offices or care homes. We aim to interview 10 staff members from VR companies and 10 care home staff. This sample size is well-suited for qualitative research, informed by literature indicating that saturation is often achieved after 9–17 interviews.^44^

Participants will be senior care home staff who have used VR training or staff from companies that provide VR training to care homes, and who are proficient in speaking and reading English, based anywhere in the UK.

We will recruit participants through various channels, including company websites, news articles, snowball sampling (referrals from other participants) and our networks, such as the PPIE group and Greater Manchester Integrated Care Board (GM ICB). Email invites will contain a study summary and the participant information sheet. We will follow-up with participants no more than two times.

#### Procedures

Consent will be obtained in writing or verbally, depending on the interview format. Participants can share their contact information (eg, email address) to receive project updates, including lay summaries and a £20 voucher as a token of appreciation.

The interviews will be semi-structured and audio-recorded for analysis. Each interview will last no more than 1 hour. A bespoke interview schedule will be developed for each set of interviews (VR company staff and care home staff). Both will start by covering employment activities, role and experience with VR. The interviews with senior care staff will explore contextual and organisational issues that must be incorporated into the training package and toolkit, and explore how care homes record data on falls and infections (for phase 2). Interviews with the staff from VR companies will help us understand their cost models and the resources they provide alongside the training to support use and uptake (eg, training guides, pre-training scenarios and structured communications with care homes). If possible, we will seek to obtain documentary evidence of related resources to inform our training materials.

#### Analysis

All data collected will be digitised, anonymised, stored and managed in an NVivo file accessible to the qualitative researchers. The qualitative researchers will analyse the data iteratively and concurrently with data collection, allowing arising topics to be explored in subsequent interviews. As earlier, thematic analysis will be used, following the four steps to integration.^43^

The findings will inform the development of the toolkit, including what form it will take and what the content will be. We will also draw on the responses from participants taking part in the testing phases. Once developed, the toolkit will be tested along with the intervention in the third round of testing.

### Phase 2: pilot study with process evaluation to explore VR training and develop the measures and methods to inform an RCT

We will conduct a mixed-methods pilot cluster RCT with a waitlist control and embedded process evaluation (to address objectives 2–4). There is a 3-month follow-up time point in addition to data collected at baseline and after the intervention (VR training).

The pilot cluster trial will test the feasibility of conducting a larger RCT, focusing on the measures and methods of evaluating the outcomes and reactions to the training (including cyber-sickness and the care home culture). The intervention will be the VR training package plus the implementation toolkit. The control group will not have any intervention but will be a waitlist control. The waitlist control allows the control group to access the training at the end of their follow-up period.

The process evaluation will generate knowledge about VR as a training mechanism in care homes, focusing on the practicality of using VR, contextual considerations and how it might be scaled up in the future.

#### Pilot cluster RCT

##### Setting, participants, recruitment and randomisation

Six care homes in North England will be recruited purposively to reflect the diversity of care homes in the UK. We will seek representation from care homes by different types (nursing, residential or mixed), size (number of beds), ownership (independent vs chain; private, charity or public) and location (deprivation).

We will recruit two small (1–50 beds), two medium-sized (51–100 beds) and two large (101–250 beds) care homes. A total of 80 staff will be recruited: 5 from each small care home, 15 from each medium home and 20 from each large home. The sample size has been selected to allow a sufficient number of repetitions of the protocols to identify any barriers and to permit assessment of feasibility outcomes.

Participants will meet all of the following inclusion criteria to take part:

Be an unregistered staff member employed at the care home, providing direct care to residents.Read and write in English.Not have previous health conditions that render them ineligible to use a VR headset due to safety reasons (eg, history of seizures).

Registered staff (eg, nurses), those unable to read/write in English or who do not provide care (eg, domestic staff or chefs) will be excluded. Randomisation will be stratified by the size of the care home, as measured by the number of beds (small (1–50 beds), medium-sized (51–100 beds) and large (101–250 beds)). Each study arm will contain one large, one medium and one small care home. All staff participants at a single site will be recruited before site allocation is revealed to ensure prospective concealment of the randomisation sequence. The randomisation sequence will be created by a study statistician, and each allocation will be revealed only after all staff participants at a site have been unambiguously enrolled in the study.

To reduce participant burden, all activities will be conducted during work hours (with the manager’s support) and on-site at the care homes, in private rooms. This may include an empty resident room, an activities room or a staff room. The researchers will be present on-site to conduct the study, meaning they can be flexible in rescheduling sessions if care work arises.

Staff will be recruited directly via the managers and senior care staff. They will identify all care staff who meet the eligibility criteria and will provide them with a written participant information sheet.

Only the intervention group will receive the VR risk reduction training with the toolkit during the trial period. Outcome data will be compared between groups. At the end of the study period, we will give the three care homes in the control group the opportunity to test the training. This is to encourage their initial participation and ensure that their staff can also benefit from the intervention.

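### Site-by-site release of allocations, in size strata of two homes split one per arm, guarantees concealment only for the first home in each stratum

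*Protocol article*

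**What the plan says.** All the rules are in the protocol article, Phase 2, Pilot cluster RCT, under Setting, participants, recruitment and randomisation.

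- Homes: "We will recruit two small (1–50 beds), two medium-sized (51–100 beds) and two large (101–250 beds) care homes".
- Staff: "A total of 80 staff will be recruited: 5 from each small care home, 15 from each medium home and 20 from each large home".
- Stratification: "Randomisation will be stratified by the size of the care home, as measured by the number of beds".
- Forced split: "Each study arm will contain one large, one medium and one small care home".
- Release rule and its purpose: "All staff participants at a single site will be recruited before site allocation is revealed to ensure prospective concealment of the randomisation sequence". The section then repeats that "each allocation will be revealed only after all staff participants at a site have been unambiguously enrolled in the study".
- Choice of homes: "Six care homes in North England will be recruited purposively".
- Route to staff: "Staff will be recruited directly via the managers and senior care staff".

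The Procedures section adds that the research team takes consent. The article does not say whether the two homes in a stratum recruit one after the other or in parallel, and nothing makes one home's release wait for the other.

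**The concern.** Three rules, each reasonable alone, combine badly: strata of exactly two clusters, a compulsory one-to-one split within each stratum, and release triggered by enrolment at one site. Together they form a block of two with sequential unmasking. The first home in a stratum is properly concealed. Once its arm is revealed, its partner's arm is no longer random to anyone who knows the pairing, whether or not it has been formally announced.

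In a cluster trial, concealment protects against differential recruitment of individuals after the cluster's arm is known. Training now and training after a wait are different offers, so who is encouraged and who agrees can vary with a known arm. If the second home has not yet been signed up, the purposive choice of home can vary with it too. The Analysis section compares hand hygiene and falls skills between groups, at a 10% significance level, to judge how promising the intervention is. Adjustment for baseline score does not remove differences in motivation that the score fails to capture. The pilot also exists to develop methods for a full trial, so a weak release procedure could be copied into it.

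**Working it through.** **Inputs** (all from Setting, participants, recruitment and randomisation): two homes in each of three size strata; 5, 15 and 20 staff per small, medium and large home; one home of each size per arm; release once a single site's staff are enrolled. One input is not given and is treated as an assumption: f, the fraction of the second home's staff already enrolled when the first home in its stratum is revealed, with range 0 to 1.

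**Step 1: the article's own total.** 2 × (5 + 15 + 20) = 2 × 40 = 80. This matches the stated 80.

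**Step 2: possible allocations.** Each stratum can be split in 2 ways, so there are 2 × 2 × 2 = 8 allocations. Each puts 5 + 15 + 20 = 40 staff in each arm.

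**Step 3: fully sequential recruitment with site-by-site release.** Six homes can be recruited in 6! = 720 orders, giving 720 × 8 = 5,760 combinations of order and allocation. Enumerating all of them, and counting the homes whose arm is already fixed by earlier reveals, gives the same answer every time: 3 of 6 homes (one per stratum) and 5 + 15 + 20 = 40 of 80 staff. Order does not matter, because the second home in a stratum is always determined by the first and never by another stratum.

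**Step 4: overlapping recruitment.** Only staff not yet enrolled at the first reveal are exposed. With the same f in every stratum:

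exposed staff = (5 + 15 + 20) × (1 − f) = 40 × (1 − f)

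| f | Exposed staff, of 80 |
|---|---|
| 0 | 40 |
| 0.25 | 30 |
| 0.5 | 20 |
| 0.75 | 10 |
| 1 | 0 |

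If overlap differs by stratum, the sum is 5(1 − f_small) + 15(1 − f_medium) + 20(1 − f_large). For example, if only the large pair is fully sequential and the other pairs finish before any reveal, 20 staff are exposed.

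**Step 5: release by pair.** If neither home in a stratum is revealed until both have finished enrolling, f = 1 by rule, so 0 of 6 homes and 0 of 80 staff are exposed. Information does not leak between strata: after the small and medium pairs have been revealed, a given large home can still be in either arm.

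**The case against.** The strongest reply is that the text sets an earliest time for release, not a timetable. Holding every allocation until a pair, or all six homes, has enrolled would already comply. This stands, and it is why the exposure is a range. A reader might infer that the second home in every stratum will be recruited with its arm known. The article does not support that, because it gives no recruitment order. What remains is that nothing requires joint release, the rule is written for one site at a time, and concealment should not depend on unstated scheduling.

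A reader might also infer that managers, knowing the arm, will hand-pick staff. The article does not say that one home's managers learn another home's allocation or the pairing, and it asks them to identify every eligible care worker. Some discretion remains, since only 5, 15 or 20 staff per home take part, but certain deduction belongs chiefly to the research team.

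Two further inferences should not be drawn. The release rule does not mention the baseline skill test, but nothing places that test after release, and a condensed article may leave the order to the full protocol. Nor would predictable allocation distort a staff-recruitment progression criterion: Table 3 has none. Its recruitment row counts homes, and the article gives no basis for saying that participant retention would cross a threshold for this reason.

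Finally, this is a six-home pilot sized for feasibility, and no progression criterion rests on an efficacy result. That stands and limits the severity.

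**Conclusion.** The point holds in conditional form. The release rule cannot by itself deliver its stated purpose: it guarantees concealment for the first home in each stratum and leaves the second to scheduling. Exposure lies between 0 and 40 of 80 staff. The upper end, covering 3 of 6 homes, requires each second home to start enrolling only after its partner is revealed; the lower end requires both homes to finish first. The range assumes that whoever makes the deduction knows the stratum pairing and the first home's arm, as the research team plausibly would. The figures count staff whose arm is deducible, not the size of any resulting bias, which the article gives no means of estimating.

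Severity is moderate. The consequences are possible recruitment bias in the skill comparison and carry-over of the procedure into the full trial.

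**What to change.** Replace the site-level release rule with one at stratum level, for example: *The study statistician will hold the sequence and release the allocations of both homes in a size stratum together, only when staff enrolment is complete in both.* Releasing all six at once also works.

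This brings the exposure to zero without changing the stratification, the one-per-arm split or the sample size. It costs one sentence, and the article says that phase 2 ethics approval is still to be sought, so it can go into that submission.

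The practical cost is waiting. The first home in each pair is held until the second has enrolled, which may lengthen its gap between enrolment and training and lose some enrolled staff; the Introduction cites a 28.3% turnover rate in health and social care for 2022/2023. Recruiting paired homes in parallel keeps the wait short. Releasing all six together would make the earliest homes wait longest, so release by pair is the lighter option.

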##### Procedures

The research team will take verbal or written consent prior to participation. During the consent process, participants will be asked whether they would like to share their contact information to receive updates on the project (eg, lay summaries). For resident falls and infections data, we will obtain consent at the care home level, as we are not collecting identifiable information.

All staff participants will receive shopping vouchers for their time. They will receive a £20 voucher after the first session and a second £20 voucher at the end of the 3-month follow-up session. Each session should not take more than 1 hour.

Table 2 presents the data we will collect/record using bespoke and validated questionnaires, observations and system data.

**Table 2 T2:** Data to be collected during the pilot cluster RCT

**Baseline**	
*Contextual participant and care home-level data*	
Contextual data	Staff demographics, role and years working in care homes
	Care home size
	Type: residential/nursing
	Indices of Multiple Deprivation score
	Care Quality Commission quality rating and specialities
	Technical infrastructure (eg, availability of WiFi, access to computers/remote devices, etc)
	Previous training delivered and cost model
**Feasibility outcomes**	
Trial feasibility	Recruitment and retention of sites and participants, as well as the number and % of staff trained. Reasons given for declining to participate (if applicable)
Training completion	Number and % of training sessions completed, and time taken
Observations	Qualitative observations (field notes taken by the researchers) on reactions, management policies, practices and care home culture and fidelity with the training schedule (considering the logic model from phase 1) to assess whether activities ran as planned
Cybersickness (post-training)	Validated and existing CSQ-VR^39 40^ to explore adverse effects related to using a VR headset (eg, fatigue or nausea)
**Candidate primary outcomes**	
*Learning impacts (at baseline, after the training for the intervention group and after 3 months post-training)*	
Knowledge	Amend the WHO Hand Hygiene Knowledge Questionnaire for Healthcare workers^53^ and the Singapore Ministry of Health Nursing Clinical Practice Guidelines on Prevention of Falls in Hospitals and Long Term Care Institutions^54^ to align with care home practices
Skill	Hand hygiene will be video-recorded and compared with the WHO six poses.^55^ Participants will identify fall risks in a picture of a simulated room. We will use multiple scenarios which are similar in difficulty to reduce any potential for contamination. The measure will be developed by drawing on the expert knowledge of our research team in falls prevention, using the current evidence base for care homes. When developing this, we will ensure to test the face validity of the measure. The scenarios may draw on the 4 P’s (or similar), which include: Pain: whether the resident is experiencing discomfort which may affect balance or mobility. Personal needs: whether residents need the toilet or other personal care as urgency can lead to rushing and unsafe movements. Position: checking residents are positioned safely—seated, standing or moving in a stable way. This also includes considering circulation or blood pressure changes and whether any equipment they need (eg, Zimmer frames) works and is within reach. Place: checking the care home environment for hazards like rugs, clutter or poor lighting
Self-efficacy	Amend items from our previous study,^23^ as existing task-specific scales are irrelevant to hand hygiene or falls
**Secondary outcomes**	
*Resident impacts (at baseline and after 3 months post-training)*	
Resident impacts	Depending on the findings from phase 1, we will collect data on falls reports and falls-related hospital admissions, emergency department (ED) attendance, GP callouts, outbreaks of infectious diseases and medication changes (antibiotic use) to help determine the feasibility of assessing impacts in a future RCT
*Employment (at baseline and after 3 months)*	
Employment	Staff satisfaction using a validated survey, for example, Job Satisfaction Questionnaire (JS-Q)^45^ or Satisfaction of Employees in Healthcare (SEHC)^46^
	Staff retention and recruitment. Staff illness and any management changes
*Cost data*	
Intervention (and health and social care) costs	Intervention costs will be calculated by micro-costing the resources used during the VR training development, adoption and delivery and split into non-recurrent and recurrent costs. A Client Service Receipt Inventory will record resident falls and infection-related numbers of inpatient hospital days, ED attendances and GP callouts. This data will help determine the cost of healthcare use in the intervention and control group care home residents

CSQ-VR, 6-item Cybersickness in VR Questionnaire; GP, general practitioner; RCT, randomised controlled trial; VR, virtual reality.

We envision the data to be counts of the number of instances of an outcome over the study period. Part of the feasibility study will involve exploring how to collect this data effectively. For example, this could include receiving reports on outcomes from the care home, auditing resident data or asking care homes to provide data into a secure data capture portal (eg, REDCap).

##### Analysis

Where relevant (eg, for the contextual care home-level data, some feasibility outcomes, primary candidate outcomes, resident impacts and staff retention and recruitment data), quantitative data will be analysed using descriptive statistics (eg, mean, sums, SD, percentages). The promise of the intervention will be assessed by comparing hand hygiene and falls skills between the groups, adjusting for clustering and the baseline score using analysis of covariance to increase power. A significance level of 10% will be used.

Analysis of validated surveys will adhere to guidelines. A total score and sub-scores for the nausea, disorientation and oculomotor symptoms will be produced for the CSQ-VR.^39 40^ The sub-scores will be calculated by adding the responses (Likert scale: 1–7) to the two questions related to each symptom. The total score is the sum of the sub-scores. Similarly, for the JS-Q,^45^ a total score and sub-score can be generated by adding the responses (Likert scale 1–5) to each item within the eight domains and calculating a total score, with higher scores indicating better job satisfaction. The Satisfaction of Employees in Healthcare^46^ is analysed by calculating a mean score of the 18 items, with higher scores reflecting higher levels of satisfaction.

Although data on costs and a range of potential outcome measures will be collected, a definitive economic evaluation will not be performed. Summary statistics will be presented for cost and outcomes data, including rates of missing data. These measures will help inform the methods for an economic evaluation of VR training in the future RCT.

Qualitative data gathered through written observations will be analysed using NVivo. The observations will be analysed using a content synthesis approach to help identify commonalities among participant reactions to using VR and the care home culture, while making comparisons to the logic model (phase 1)gives a deeper understanding of whether (and how) the activities ran as planned.

### Process evaluation

Process evaluations should be a collaborative approach, so the PPIE group and relevant stakeholders will be engaged to:

Develop and verify the logic model for the intervention. Logic models can prioritise and structure research questions and data collection to help explain how the intervention works to achieve its outcomes or why it does not always work.Refine and prioritise the process evaluation’s primary and secondary research questions. The research questions will build on the literature and previous work, and these might include questions around:Adherence to the intended delivery of the VR training.Adaptations made to deliver the VR training in different settings.What staff groups do or do not engage with the VR training.How the VR training is perceived among different stakeholders.We will refine and test the initial logic model for the different sites to understand similarities and differences in the contexts, relationships and environments that may shape the implementation of the VR training.

Insights from meetings conducted with the PPIE group, combined with data collected in phase 1, will help us understand the implementation of the training in the future.

